## Abstract

**Background:**

Patients with chronic low back pain (CLBP) suffer with functional, social, and psychological aspects. There is a growing number of studies with multimodal approaches in the management of these patients, combining physical and behavioral therapies such as osteopathic manipulative treatment, associating pain education and clinical hypnosis. The aim of the present study will be to evaluate the effects of osteopathic manipulative treatment (OMT) associated with pain neuroscience education (PNE) and clinical hypnosis (CH) on pain and disability in participants with CLBP compared to PNE, CH, and sham therapy.

**Methods:**

A randomized controlled clinical trial will be conducted in participants aged 20–60 years with CLBP who will be divided into two groups. Group 1 will receive PNE and CH associated with OMT, and G2 will receive PNE, CH, and sham therapy. In both groups, 4 interventions of a maximum of 50 min and with an interval of 7 days will be performed. As primary outcomes, pain (numerical pain scale), pressure pain threshold (pressure algometer), and disability (Oswestry Disability Questionnaire) will be evaluated and, as a secondary outcome, global impression of improvement (Percent of Improvement Scale), central sensitization (Central Sensitization Questionnaire), biopsychosocial aspects (Start Beck Toll Questionnaire), and behavior of the autonomic nervous system (heart rate variability) will be assessed. Participants will be evaluated in the pre-intervention moments, immediately after the end of the protocol and 4 weeks after the procedures. Randomization will be created through a simple randomized sequence and the evaluator will be blinded to the allocation of intervention groups.

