### Outcomes

Participants will be evaluated by a researcher blind to allocation and the evaluative moments for all outcomes will correspond to the pre-intervention (M0), immediately after the last meeting (M1) and reassessed again in the follow-up of four (M2) weeks after the end of the protocols (Fig. 2).

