#### Main outcome

Pain and disability will be the main outcomes of the study. Pain will be evaluated through the numerical pain scale, where the participant will be asked about their perception of pain suffered in the last week and will assign a value to it, ranging from 0 to 10, where 0 indicates no pain and 10 indicates worst pain ever felt [11, 23]. Pain will also be assessed by pressure threshold using a pressure algometer device (Fnd-50, PIAB 50-n, Italy) in the lumbar region. The assessment will be conducted specifically on the paraspinal muscles bilaterally at the L1 to L5 levels. Three measurements will be performed at the same point, and the average of the values will be calculated [24]. The distal end of the device will be positioned perpendicularly on the evaluated surface, and constant pressure of 2.55 kg will be applied. Participants will be instructed to indicate the moment when the sensation of pressure changes to a sensation of pain and the value will be recorded. The pain threshold will be defined in kilogram-force (kgf/cm^2^), through the minimum pressure necessary to induce pain in the evaluated region. Still as the main outcome, disability will be evaluated through the Oswestry Disability Questionnaire translated and validated for the Brazilian population [25] composed of ten questions that assess pain intensity and the effect of pain on activities of daily living and classify the individual as minimal (0–20%), moderate (21–40%), severe (41–60%), disability (61–80%), or bed-bound (81–100%) [26].

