### Sample size

The sample size was calculated to detect an effect between groups for the pain intensity outcome assessed using the numerical scale. For the calculation, a power of 80% and an alpha error of 5% were adopted and, based on the results obtained by Rizzo et al. [11], a standard deviation of 2.0 points and an average difference of 1.3 points were considered, which resulted in a total sample size of 52 individuals. Considering possible sample losses, there will be an increase of 15% in the sample size calculated, totalizing 60 participants. All calculations were performed on the software G*Power version 3.1.9.7 [34].

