### Statistical analysis

To analyze the population profile data, we will use the descriptive statistical method and the results will be presented with mean values, medians, standard deviations, minimum and maximum values, and confidence intervals.

Data normality will be determined using the Shapiro-Wilk test, and the comparison of variables between groups at baseline will be performed using Student’s *t*-test for unpaired data for data with normal distribution or the Mann-Whitney test for non-normal data.

Comparisons of primary and secondary outcomes between groups and moments will be performed using the analysis of variance technique for repeated measures model in the two-factor scheme. Repeat measurement data will be checked for sphericity violation using Mauchly’s test, and the Greenhouse-Geisser correction will be used when sphericity is violated.

To analyze the moments, Bonferroni’s post-test for normal distribution or Dunnet’s post-test for non-normal distribution will be used, and the analysis of the different moments between the groups will be carried out using Student’s *t*-test for unpaired data with normal distribution or Mann-Whitney test for non-normal data.

The adopted statistical significance will be set at 5%. Analyses will be performed using the Statistical Package for the Social Sciences software—version 22.0 (SPSS Inc., Chicago, IL, USA) by a researcher blinded to treatments and group allocations using a coded spreadsheet. All the randomized participants will be included in the analysis, in accordance with intention-to-treat principles. To consider all participants, the missing data will be addressed according to the last observation carried forward (M0 or M1) [36]. Analysis and results from this study will be conducted by an independent biostatistician and checked for accuracy.

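### Three primary outcomes are compared between groups at two moments at an unadjusted 5%, with no single primary endpoint and no success rule

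*Protocol article*

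**What the plan says.** The abstract lists three primary measures: "As primary outcomes, pain (numerical pain scale), pressure pain threshold (pressure algometer), and disability (Oswestry Disability Questionnaire) will be evaluated". The Main outcome section agrees. It opens with "Pain and disability will be the main outcomes of the study", then adds "Pain will also be assessed by pressure threshold using a pressure algometer device", and describes the Oswestry score as a main outcome too.

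The Outcomes section applies the same schedule to every outcome: baseline (M0), then "immediately after the last meeting (M1) and reassessed again in the follow-up of four (M2) weeks after the end of the protocols". Neither post-treatment moment is called primary.

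The Statistical analysis section plans a two-factor repeated-measures ANOVA for each outcome. It then plans post-tests between moments (Bonferroni, or a named alternative for non-normal data) and unpaired t or Mann-Whitney tests between groups at the different moments. One level is given for everything: "The adopted statistical significance will be set at 5" per cent.

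The Sample size section rests on one outcome only: "The sample size was calculated to detect an effect between groups for the pain intensity outcome assessed using the numerical scale". It names no moment.

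**The concern.** The plan has three primary measures and two post-treatment moments, so it offers six between-group comparisons of primary status. The only multiplicity correction concerns comparisons of moments; it reaches neither the three outcomes nor the between-group tests. The Background asks whether OMT adds benefit for pain and disability in the short and medium terms, but no section says which result, or which combination, answers that question. One isolated significant result out of six could therefore be reported as success on a primary outcome.

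The timing of the numerical scale bears on which moment to choose. It asks about "perception of pain suffered in the last week". M1 follows directly after session 4, and sessions are at least seven days apart, so most of the week recalled at M1 lies before that session. At M2 the recalled week lies wholly after treatment.

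**Working it through.** **The plan's own figure.** The article gives no familywise error rate, so there is none to reproduce. The sample size of 52 can be recovered and is used under the fix. The standardised difference is d = 1.3/2.0 = 0.65, so f = 0.325. In a repeated-measures between-groups F test with m = 3 moments and an assumed correlation of 0.5, the noncentrality is f² × N × m / (1 + (m − 1) × 0.5) = 0.1056 × 52 × 3 / 2 = 8.24, which gives power 0.804. Adding 15% gives 52 × 1.15 = 59.8, hence 60.

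**Inputs.** Three primary outcomes (abstract; Main outcome); two post-treatment moments (Outcomes); 5% per test (Statistical analysis), taken as two-sided because the text does not say. Algometry is counted as one value per participant. It is measured on both sides at L1 to L5 without a stated way of combining sites, so six tests may be an undercount. The correlations are assumptions; the documents give none.

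**Step 1: six by-moment tests, independent.**
- Any false difference, either direction: 1 − 0.95^6 = 0.265.
- At least one false difference favouring OMT: 1 − 0.975^6 = 0.141.

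**Step 2: six by-moment tests, correlated** (multivariate normal, 300,000 draws, no true effect):

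| Correlation between outcomes | Correlation between moments | Either direction | Favouring OMT |
|---|---|---|---|
| 0.3 | 0.5 | 0.237 | 0.120 |
| 0.3 | 0.7 | 0.221 | 0.111 |
| 0.5 | 0.5 | 0.221 | 0.111 |
| 0.5 | 0.7 | 0.202 | 0.100 |
| 0.7 | 0.5 | 0.192 | 0.096 |
| 0.7 | 0.8 | 0.166 | 0.083 |

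**Step 3: one omnibus test per outcome.** Independent: 1 − 0.95^3 = 0.143. With correlation 0.3 between outcomes: 0.136. With 0.5: 0.125.

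**Step 4: by-moment tests counted only after a significant group-by-moment interaction** (20,000 simulated trials, 30 per arm; correlations 0 to 0.5 between outcomes and 0.5 or 0.7 between moments): 0.031 to 0.048.

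**Comparison.** One outcome at one moment gives 5% in either direction, and 2.5% favouring OMT. The six tests give about 10-14% favouring OMT, which is 0.100/0.025 = 4.0 to 0.141/0.025 = 5.6 times as much.

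**The case against.** Several counter-arguments carry weight.

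- **Direction.** A reader might take 20-26% as the chance of wrongly declaring OMT effective. It is not: it counts differences in either direction, including those favouring sham. The figure for a false OMT benefit is about half that.
- **Gating.** The unpaired tests are described after the ANOVA and can be read as follow-up to it. If they counted only after a significant interaction, the rate would be about 3-5%. This is a possible reading, but the Statistical analysis section states no such condition, and it plans the ANOVA separately for each primary outcome.
- **Success rule.** If every primary outcome had to succeed, there would be no inflation. The hypothesis does join pain with disability and the short with the medium term, but the article does not make joint success a requirement. It does not say that any one result suffices either, so the rates above depend on that assumption.
- **The 5% level.** A reader might say that the protocol breaks its own promise of 5% overall. The text sets a significance level and claims no familywise rate.
- **Timing.** A reader might infer that session 4 cannot affect the M1 pain score. That is too strong: the rating is given after the session, and a recalled perception may be coloured by the participant's state when answering. The recall window is also the same in both arms. The point bears on the choice of moment and adds nothing to the error rate.
- **Analysis plan.** Gating and multiplicity detail may sit in an analysis plan that is not shown. That is fair for those details. Naming the primary outcome and moment belongs in the protocol, and the article does set out its tests and level. Powering on the numerical scale points to a candidate but does not designate it.

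**Conclusion.** The point holds. The plan has three primary outcomes and two moments, with no single primary endpoint, no primary moment and no success rule; nothing is adjusted across outcomes or between-group tests.

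The size depends on which tests count. If any one significant result is success, the chance of at least one false group difference in either direction is:
- about 20-26% over six ungated by-moment tests, falling to about 17-19% at stronger correlations;
- about 12-14% with one omnibus test per outcome.

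A false result favouring OMT has a chance of about 10-14% over the six tests (8-10% at the stronger correlations), against 2.5% for one two-sided test. The direction of the problem is secure. The exact rate is not, because the correlations, the gating and the success rule are all unstated.

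**What to change.** Before the analyst sees the allocation code, name the between-group difference in the numerical pain scale at one moment as the single primary endpoint. It is already the powered outcome. M2 is a reasonable moment because its recall week lies wholly after treatment, though the choice is the investigators'. Test Oswestry and then pressure threshold at that same moment, in that order, each at 5%, stopping at the first non-significant result. This holds the confirmatory error rate at 5%. Report the other moment as secondary, and update the protocol and the registry.

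**Cost.** No extra participants or visits are needed to control the error rate. By contrast, Bonferroni over three outcomes (0.05/3 = 0.0167 each) would raise the total before losses from 52 to 70 by the formula that recovers 52. The price of the fixed order is that Oswestry and threshold results are confirmatory only if the numerical scale succeeds first.

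The sample size paragraph should then be matched to the named moment. For the stated 1.3 points and SD 2.0, an unadjusted two-sided comparison at one moment has about 71% power with 30 per arm. With adjustment for baseline at an assumed correlation of 0.5, it needs 76 × (1 − 0.25) = 57, so 58 in equal arms.

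Leave the M1 visit where it is. Recruitment began in November 2021, and moving a visit would be a schedule change in a running trial.

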**Discussion:**

The guidelines have been encouraging multimodal, biopsychosocial approaches for patients with CLBP; in this sense, the results of this study can help clinicians and researchers in the implementation of a model of treatment strategy for these patients. In addition, patients may benefit from approaches with minimal risk of deleterious effects and low cost. In addition, it will enable the addition of relevant elements to the literature, with approaches that interact and do not segment the body and brain of patients with CLBP, allowing new studies in this scenario.

**Trials registration:**

Date: September 4, 2021/Number: NCT05042115.

## Background

Low back pain (LBP) stands out as the main cause of disability and for the decrease in world productivity within 354 medical conditions evaluated [1]. The chronification of these cases, in addition to the socioeconomic impacts, is characterized by a complex interaction of biological, social, and psychological factors [1, 2]. In Brazil, the prevalence of CLBP is increasing [3], with findings ranging from 10 to 50% in different populations [4], which can result in a higher prevalence of disability and functional limitations, especially in the economically active population, contributing to negative socioeconomic impacts. Carregaro et al. [5] highlighted that in countries such as Brazil, between 2012 and 2016, about US$ 2.2 billion was spent on CLBP, with 79% of this amount spent on productivity losses, in addition the authors point out that in the same period more than 880,000 imaging exams were performed, and that these individuals missed work 59 million days in that period. These data reinforce the need for improvements in health services and policies to deal with this dysfunction, as well as strategies to reduce the widespread use of diagnostic imaging.

Treatment options that address only single etiologic conditions have been shown to be ineffective. Therefore, multimodal and multidisciplinary approaches to the management of chronic low back pain (CLBP) have been encouraged [6].

Guidelines point out as main treatments for LBP approaches with exercises, education, and manual therapy. Strong evidence recommends aerobic and strength exercise modalities for CLBP, as they promote the resumption of physical capacities and gradual exposure of patients to movements. On the other hand, the education of individuals with CLBP aims to help understand the causes and factors that influence pain intensity, in addition to promoting knowledge about available treatment strategies. Finally, manual therapy can also compose the treatment of this individual, since it allows improvement in movement and spinal stiffness in patients with CLBP [7]. Thus, there is a growing number of clinical trials investigating multimodal approaches in patients with chronic pain.

Osteopathic manipulative treatment (OMT) is a hand-on part of osteopathic approach and a modality used in the treatment of LBP. Dal Farra et al., in a meta-analysis, presented strong evidence on pain reduction and improvement in function in LBP patients undergoing OMT [8]. The results presented by the systematic review by Louw et al. showed that, combining movement therapies, such as manual therapies, with education processes, it potentiated the effects on pain, function, disability, and psychosocial factors and also enabled improvement in movements and decreased use of health services in patients with chronic musculoskeletal pain [9].

Buttler and Moseley developed a method called pain neuroscience education (PNE). Addressing concepts of neurophysiology, neurobiology, representation, and meaning of pain, PNE aims to desensitize the neural system, contrary to the traditional anatomical and biomedical model [10]. In association with educational strategies, Rizzo et al. showed that clinical hypnosis (CH) enhances the results of education processes in patients with CLBP in the short and medium terms [11]. Thompson et al. in a meta-analysis totaling 3632 patients showed the effectiveness of CH as a pain re-education technique, producing moderate to great analgesia for all pain outcomes [12].

In view of the absence of standards in isolated allopathic or complementary treatments in the effectiveness of the treatment of CLBP, the growing number of researches in these areas of activity, and the absence of high-quality clinical trials that combine the aforementioned therapies in the management of this condition, our research is justified. This study aims to know whether OMT associated with PNE and CH is effective in the pain and disability of patients with CLBP in the short and medium terms or if the PNE and CH are sufficient in the management of these patients. We hypothesize that the combination of a physical approach such as OMT with PNE and CH can bring more benefits to this population, improving pain levels and reducing disabilities, in the short and medium terms.

## Objectives

### Primary objective

The primary objective of the present study will be to evaluate the effects of PNE and CH associated with OMT on pain and disability in patients with CLBP compared to PNE and CH associated with sham therapy.

### Secondary objective

The secondary objectives will be to evaluate the effects of PNE and CH associated with OMT on patient's global impression of improvement, central sensitization, biopsychosocial factors, and the modulation of the autonomic nervous system.

## Methods

### Study design and participants

This protocol is a randomized, parallel-group, evaluator-blind, sham-controlled clinical trial, with an allocation ratio of 1:1, prospectively registered at ClinicalTrials.gov (NCT NCT05042115) on September 4, 2021, and follows SPIRIT 2013 and TIDiER-placebo recommendations [13, 14] for clinical trials.

Individuals diagnosed with nonspecific CLBP for at least 3 months will be included, with a mean numerical pain scale (NPE) score of at least 3 points and aged between 20 and 60 years [11]. Individuals undergoing concomitant physiotherapeutic treatment, individuals with medical contraindication to exercise, smokers/alcoholics, severe vertebral or neural pathologies, previous spine surgeries, cardiorespiratory disease, CLBP as a secondary complaint, pregnancy, hearing problems, or illiteracy and those who present an increase in symptoms in the stages of the study will be excluded.

On the day of the initial assessment (M0), all eligible participants will be informed about the procedures and objectives of the study and, after agreeing, they will sign an informed consent form (ICF), being able to voluntarily interrupt their participation in the study at any experiment stage. All study procedures were approved by the Research Ethics Committee at State University of the North of Paraná - UENP (CAEE: 43063621.3.0000.8123) and followed the Declaration of Helsinki.

The procedures will be carried out in reserved rooms of the same clinic in order to avoid any type of exposure or possible embarrassment to the participants. In the event of the possibility or presence of any type of real or potential embarrassment perceived by the participants or researchers, the intervention will be stopped immediately. All procedures will be conducted by the researcher ([name]) with experience of more than 7 years in the proposed procedures, and the evaluation will be conducted by one professional of clinical physiotherapy at the State University of the North of Paraná, previously trained in outcomes measurement. To characterize the participants, the following data will be collected: gender, age, duration of pain (months), weight, height, physical activeness, and use of medication.

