### Allocation—sequence generation

A simple randomized sequence will be created via the www.randomization.com website by a contributor external to the researchers directly involved in the research. After the initial assessment, the researcher will access the randomization envelope and carry out the intervention according to the group allocation indicated on the envelope, that is, group 1 PNE+CH+OMT or G2 PNE + CH + sham therapy.

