### Blinding

The person responsible for evaluating the outcome measures will be blinded to the allocation of intervention groups. Given the nature of the study, it is impossible to blind the researcher/therapist. At the end of the protocol, participants will be asked to report on which type of manual therapy was assigned to their treatment (sham or OMT), in order to assess blinding success [35].

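### The exclusion of participants whose symptoms increase during the study acts after randomisation, is undefined, and conflicts with the rule that everyone randomised is analysed

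*Protocol article*

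**What the plan says.** The sentence in Study design and participants that lists baseline exclusions (previous spine surgery, pregnancy, concomitant physiotherapy and others) ends by saying that "those who present an increase in symptoms in the stages of the study will be excluded". No scale, threshold, time window or assessor is given for the increase.

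Allocation—sequence generation fixes the order of events: "After the initial assessment, the researcher will access the randomization envelope and carry out the intervention according to the group allocation". No run-in is described. Under Outcomes, assessments take place before the intervention (M0), "immediately after the last meeting (M1) and reassessed again in the follow-up of four (M2) weeks after the end of the protocols".

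Main outcome states that "Pain and disability will be the main outcomes of the study".

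Statistical analysis states that "All the randomized participants will be included in the analysis, in accordance with intention-to-treat principles", and for gaps in the data that "the missing data will be addressed according to the last observation carried forward (M0 or M1").

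Blinding says of the person delivering treatment that "it is impossible to blind the researcher/therapist".

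**The concern.** With no period between baseline and allocation, an increase in symptoms during the study can only be seen in someone already randomised. The clause is therefore a post-randomisation exclusion, although it is listed with the eligibility criteria. In a chronic low back pain trial the natural meaning of symptoms is pain and disability, so the people it removes are those likely to have the worst values on the main outcomes.

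Three things are at stake.

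- **Comparability.** Removing people on a response to treatment breaks the balance that randomisation provides, and the sections do not say whether such a person is in or out of the analysis.
- **Worsening as a result.** The global improvement scale (Secondary outcomes) runs down to −5 for much worse, and the Discussion anticipates minimal risk of harmful effects. The clause takes out the participants who would populate the lower half of that scale.
- **Uneven application.** One unblinded researcher delivers all procedures, sees each participant weekly and asks about co-interventions. An exclusion without a definition could be applied differently by arm, even without intent.

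**Working it through.** **Step 1: what each reading does to a worsened participant.** The clause carries no figure of its own, so the first check is on the text.

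| Time of exclusion | *Excluded* = removed from analysis | *Excluded* = withdrawn, last value carried |
|---|---|---|
| Before M1 | Lost, against the intention-to-treat sentence | M0 stands in for M1 and M2: worsening becomes no change |
| At M1, already worse there | Lost | M1 is observed and carried to M2: that worsening is kept |
| Between M1 and M2 | Lost | M1 stands in for M2: worsening since M1 is lost |

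Only the middle row of the last column preserves the adverse value.

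**Step 2: inputs for an illustration.**

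- From Sample size: a difference of 1.3 points and an SD of 2.0 on the pain scale. The article does not say that 2.0 is the SD of change; using it as such is an assumption. It holds if the SD is 2.0 at both times and the M0–M1 correlation is 0.5, because 2√(2(1−0.5)) = 2.
- Assumed, not in the document: normal change scores; mean improvements of 2.5 (sham) and 3.8 (OMT), or 1.5 and 2.8; any rise above M0 triggers exclusion; every exclusion happens before M1.

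**Step 3: formulas.** Let I be the improvement (M0 minus M1), normal with mean m and SD s = 2. Worsening is I < 0.

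- Share worsening: Φ(−m/s)
- Mean if the worsened are dropped: m + s·φ(m/s)/Φ(m/s)
- Mean if M0 is carried (worsening set to 0): m·Φ(m/s) + s·φ(m/s)

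**Step 4: results.**

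| m | Share worsening | Mean, dropped | Mean, M0 carried |
|---|---|---|---|
| 2.5 | 10.6% | 2.5 + 0.3653/0.8944 = 2.908 | 2.2359 + 0.3653 = 2.601 |
| 3.8 | 2.9% | 3.8 + 0.1312/0.9713 = 3.935 | 3.6909 + 0.1312 = 3.822 |
| 1.5 | 22.7% | 1.5 + 0.6023/0.7734 = 2.279 | 1.1601 + 0.6023 = 1.762 |
| 2.8 | 8.1% | 2.8 + 0.2995/0.9192 = 3.126 | 2.5739 + 0.2995 = 2.873 |

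Differences between arms, true value 1.3:

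- 2.5 and 3.8: dropped 3.935 − 2.908 = **1.03**; M0 carried 3.822 − 2.601 = **1.22**
- 1.5 and 2.8: dropped 3.126 − 2.279 = **0.85**; M0 carried 2.873 − 1.762 = **1.11**

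**Step 5: sensitivity.** With M0–M1 correlation from 0.3 to 0.7 and mean sham improvement from 0 to 2 points, the same calculation gives 0.56 to 1.07 (dropped) and 0.79 to 1.24 (M0 carried). The distortion grows as average improvement shrinks.

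**Step 6: direction.**

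- Equal means and equal SDs: both arms have the same formula and inputs, so the bias is 0.
- Equal mean improvement of 1, but change SD 3 (OMT) and 2 (sham): dropped 2.795 − 2.018 = 0.78, M0 carried 1.763 − 1.396 = 0.37. An apparent OMT benefit arises where there is none on average.
- OMT truly worse by 1.3 (means −0.3 and 1.0, SD 2): the harm shows as 2.018 − 1.492 = 0.53 (dropped) or 1.396 − 0.657 = 0.74 (M0 carried).

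**The case against.** The strongest reply is that the sections can be read together. *Excluded* may mean withdrawn from participation, with the person kept in the analysis through the last-observation rule; Study design and participants never says that data are discarded. A reader might infer that the two rules are logically incompatible, and the document does not support that. But nothing in it confirms the withdrawal reading either, and that reading still loses worsening that occurs before M1 or between M1 and M2.

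Other replies stand in part.

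- A reader might infer that the exclusion is defined on a primary outcome. The text says only symptoms, with no reference to the pain scale, the pressure threshold or the Oswestry questionnaire. The link is a strong inference and no more.
- The any-increase trigger is assumed. A rule meant for marked worsening would affect fewer people. The M0-carried figures also assume that every exclusion comes before M1, whereas someone first found worse at M1 keeps that value.
- A reader might infer that the clause conceals harm altogether. The Interventions section invites adverse-event reports at any time to any researcher, so worsening has a reporting route. It would be missing from the efficacy comparison, not necessarily from the record.
- A reader might infer a bias in favour of OMT. Step 6 shows that no direction is fixed.
- The clause may have been meant as a safety provision. Separating it from eligibility and analysis leaves that purpose untouched.

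**Conclusion.** The point holds: the clause is wrong as written. It is an undefined post-randomisation exclusion on an event close to the main outcomes, and it conflicts with the commitment to analyse everyone randomised. Under either reading, adverse values are lost selectively, and an unblinded therapist is in a position to influence which ones.

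The size cannot be known from the document, which gives no rates of worsening. For the mean improvements assumed, a true difference of 1.3 would appear as roughly 0.85 to 1.03 if worsened participants are dropped and 1.11 to 1.22 if M0 is carried. For those means and equal SDs, these are upper bounds on the distortion as regards trigger and timing. They are not the worst case over all possible mean improvements, as Step 5 shows. They rest on normal change scores with SD 2.

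The planned sample size is not affected.

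**What to change.** Reconcile Study design and participants with Statistical analysis:

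- Take the clause out of the eligibility and exclusion list.
- State that an increase in symptoms does not end follow-up and does not remove a participant from the analysis.
- Assess all randomised participants at M1 and M2 and analyse them in their randomised arm, using observed values.
- Report the number worsening by arm, with the definition of worsening used for that count.
- If the clause has already been applied to anyone (Trial status says recruitment is ongoing), report how many by arm and at what stage.

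Whether treatment continues for such a participant is a separate clinical matter for the sponsor and is not prescribed here. It needs to be stated apart from follow-up and analysis.

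The cost is a short amendment, notified by the route in Protocol amendments, and attendance at visits already scheduled. It should be made early: outcomes not collected after an exclusion cannot be recovered at the analysis stage.
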